# Risk/Benefit Assessment

## Known Potential Risks

The use of Cannabinol (CBD) and Tetrahydrocannabinol (THC) is associated with some risk of developing adverse effects of the Central Nervous System (CNS) and peripheral organ system. The most common side effects related to CBD and THC extracts are described below. Literature suggests that the incidence of less common side effects with Cannabis extract is lower in long-term studies compared to short-term (e.g., single dose) studies, which is because of the development of tolerance.

The Adverse Drug Reactions (ADRs) associated with the use of CBD and THC are described below.

**>10%**

Drowsiness (23-25%); general infections (21-25%); decreased appetite (16-22%); fatigue, weakness, and lack of energy (11-12%); diarrhea (9-20%); liver damage (8-16%); rash (7-13%); insomnia (5-11%)

**1-10%**

Irritability, agitation (5-9%); Pneumonia (5-8%); Sedation (3-6%); Anger/ aggression (3-5%); decreased weight (3-5%); infectious diarrhea (4%); Hypoxia/Respiratory failure (3%); fungal infection (1-3%)

## Known potential Benefits

The CBD-enriched CHE may help improve chronic headache symptoms, reduce the frequency of headaches, and improve the quality of life based on anecdotal and clinical experience. CBD-enriched CHE is hypothesized to improve sleep quality and physical functioning in patients suffering from the chronic headaches, however, there is a paucity of literature documenting the potential benefits of cannabis in the treatment of adolescents with chronic headaches.

# OBJECTIVES AND ENDPOINTS

| **OBJECTIVES** | **ENDPOINTS** | | **JUSTIFICATION FOR ENDPOINTS** |
| --- | --- | --- | --- |
| **Primary** | | | |
| To determine the safety and tolerability of 1:25 CBD-enriched Cannabis Herbal Extract (CHE) in adolescents with chronic headaches | The frequency and type of treatment-emergent adverse events among patients treated with CBD-enriched CHE reported daily and evaluated monthly before the subsequent dose escalation  [Time Frame: daily throughout the study] | | This is a first in human trial technically, underpowered for efficacy so primary objective is safety of CBD |
| **Secondary** | | | |
| To investigate relationships between the dose-escalation and change in the frequency of headache.  To monitor the effect of CBD-enriched CHE on the intensity of pain related to chronic headache  To evaluate the effect of CBD-enriched CHE on sleep, mood and function in adolescents with chronic headaches.  To explore the impact of chronic headaches on quality of life. | The percentage change in the number of headache-free days per month from baseline to each follow up visit  [Time Frame: monthly throughout the study]  The percentage reduction in the average daily pain intensity due to chronic headache on the Numeric Rating Scale (NRS) from baseline to each follow up visit.  [Time Frame: daily throughout the study]  Sleep, mood, and function are to be reported using the percentage change in the scores of PROMIS  (Patient Reported Outcome Measurement Information System) measures from the pediatric Item bank:   1. Pediatric Sleep-Related Impairment– Short Form 8a scale 2. Pediatric Short Form v2.0 – Anxiety – 8a scale 3. Pediatric Short Form v2.0 – Depressive Symptoms 8a scale 4. Pediatric Pain Interference – Short Form 8a scale 5. Pediatric Positive Affect – Short Form 8a and goal attainment scaling ( participant and parent-reported) 6. Self-directed goal attainment will be reported as percentage toward a physical, mental and social goal reported by participant   [Time Frame: monthly throughout the study]  Scores of PedsQL ™ Family Impact Module Version 2.0 and compared with baseline scores  [Time Frame: monthly throughout the study] | | Headache is a common symptom in patients with chronic headaches; It will be an essential measure to study the effect of CBD-enriched CHE on the incident of headache-free days  It will be helpful to evaluate the effect of CBD –enriched CHE on the intensity of pain related to chronic headache  The pain and discomfort in chronic headaches are associated with the decrease in the quality and quantity of sleep; patients are more likely to suffer from depression and anxiety and have a functional disability, absence of school; these measures will be reasonable to determine the effect of CHE on sleep, mood and physical function  These endpoints will be used to estimate the impact of a CBD- enriched CHE on quality of life. As cannabis products may affect a wide variety of symptoms, including pain, sleep, mood and function, quality of life provides an overall impact on family impact. |
| **Exploratory** **Objectives** | | | |
| To investigate the relationship between the dose-escalation and steady-state trough levels of bioactive cannabinoids  To investigate the relationship between pharmacogenetic variation and response outcomes in adolescents receiving CBD-enriched CHE | | Steady-state trough levels of bioactive cannabinoids, namely THC, CBD, 11-OH-THC, 7-OH-CBD, and Cannabichromene during each follow up visit before dose escalation  [Time Frame: monthly throughout the study]    Genetic polymorphisms of genes encoding for CYP enzymes and the p-glycoprotein transporter and plasma levels of THC, CBD and their active metabolites in the study participants | It is an important measure to study the linearity of the pharmacokinetics of the drug product to better understand who responds best and how metabolism changes overtime and between individuals.  Cannabinoid response is highly variable. This will help to get a more clear picture of variability in seen in cannabinoid pharmacokinetic and pharmacodynamic response. |

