| Endpoints | **Primary Endpoint:**  The frequency and type of treatment-emergent adverse events among participants treated with CBD-enriched CHE reported daily and evaluated monthly before the subsequent dose escalation  **Secondary Endpoints:**   1. Number of headache-free days per month. 2. Percentage change in average daily pain intensity due to headache on the numeric rating scale (NRS) from baseline to each follow up visit. 3. Sleep, mood and function are to be reported using the percentage change in the scores of PROMIS (patient-reported outcome measurement information system) measures from the Pediatric Item Bank:    1. Pediatric Sleep-related Impairment – Short Form 8a    2. Pediatric Short Form v2.0 - Anxiety - 8a    3. Pediatric Short Form v2.0 - Depressive Symptoms 8a    4. Pediatric Pain Interference – Short Form 8a    5. Pediatric Positive Affect – Short Form 8a    6. Self-directed goal attainment will be reported as a percentage toward a physical, mental and social goal reported by participants at each monthly visit. 4. Family impact scores will be reported by PedsQL™ Family Impact Module, Version 2.0 and compared with baseline scores.   **Exploratory Endpoints:**   1. Steady-state plasma levels of bioactive cannabinoids, namely THC, CBD, 11-OH-THC, 7-OH-CBD, and Cannabichromene, during each follow up visit before dose escalation. 2. Genetic polymorphisms of genes encoding for CYP enzymes and the p-glycoprotein transporter and plasma levels of THC, CBD and their active metabolites in the study participants. |
| Number of Participants | 20 participants |
| Inclusion Criteria | Adolescent patients of the qualified investigator between the ages of 14-17 years with chronic headaches will be enrolled.  They must have headaches (migraine or tension-like features) on more than 15 days per month for more than 3 months and have failed at least two treatment options for either tolerability or efficacy.  Participants must be committed to using contraception, abstaining from recreational cannabis use, and working with psychology and physiotherapy teams as appropriate. |

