# STUDY POPULATION

## Inclusion Criteria

To be eligible to participate in this study, an individual must meet all of the following criteria:

1. Adolescents aged between 14-17 years of age at the time of screening.
2. Diagnosed with Chronic Migraine according to ICHD-3: headache (migraine-like or tension-type like) occurring on 15 or more days per month for more than 3 months which on at least 8 days per month have features of migraine headache. [[121](#_heading=h.1wjtbr7)]
3. Failed at least two treatment options on the grounds of safety (tolerability) and/or efficacy, including but not limited to antidepressant (tricyclic antidepressant or selective norepinephrine reuptake inhibitor), magnesium, gabapentinoids topiramate and/or non-pharmacological therapies.
4. Females who have reached menarche should have a negative pregnancy test during screening.
5. Must be willing to engage with psychology and physiotherapy throughout the trial as appropriate.

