**Goal Attainment Scaling**

Goal attainment scaling is a patient-reported outcome measure. Goals are selected, and further goals are standardized to extend by which the study participant meets the chosen goals. Here, we aim to choose the attainment of physical, mental and social goals. In this scaling, goals are weighted with the importance multiplied by difficulty. Further, importance and difficulty are rated on a scale of 4, starting from 0 to 3; where 0 means not at all (important/difficult). 4 means very important/difficult, leading to the generation of scoring goals. Where -1 means the patient experiences difficulties in achieving that particular goal, while -2 will be the baseline rate. [[130](#_heading=h.488uthg)]

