### Baseline Descriptive Statistics

The primary statistical analysis will be a descriptive summary of the pattern of incidence and severity of adverse events across dosage levels. Conventional summary statistics will describe baseline characteristics and other outcomes (means, standard deviations, and medians, range and interquartile range (IQR) for numerical variables; counts and percentages for categorical variables). Summaries will be provided both overall and by dosage level. Medians, ranges and IQR, will be provided for the concentrations of CBD, THC and the primary metabolites at each sampling point. The ratio of parent compound concentration to metabolites will also be summarized to explore variability in cannabinoid metabolism. System organ class will present the severity, frequency, and relationship of treatment-emergent AEs to study intervention. The start date, stop date, severity, relationship, expectedness, outcome, and duration of each AE will be reported. Serious treatment-emergent AEs will be presented either in a table or a listing. The secondary outcomes, including pain, sleep impairment, depression, positive affect, anxiety and goal attainment scores, will be summarized at each timepoint; change from baseline will also be reported (both absolute and percentage change).

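### The headache-free-days endpoint is a count in the synopsis but a percentage change in the objectives table, and percentage change fails for zero baselines and for goal scores that start at -2

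*Protocol*

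**What the plan says.** - **Objectives and Endpoints table (Protocol).** The endpoint for headache frequency is "The percentage change in the number of headache-free days per month from baseline to each follow up visit".
- **Synopsis, Secondary Endpoints (Protocol).** The same endpoint is "Number of headache-free days per month", with no change and no percentage.
- **Inclusion Criteria (Protocol).** Criterion 2 asks for "headache (migraine-like or tension-type like) occurring on 15 or more days per month for more than 3 months". It sets no maximum number of headache days.
- **Goal attainment (Protocol).** In the objectives table, the list of scores reported as percentage change has as its fifth item "Pediatric Positive Affect – Short Form 8a and goal attainment scaling ( participant and parent-reported". The sixth item is a different measure: "Self-directed goal attainment will be reported as percentage toward a physical, mental and social goal reported by participant". The Goal Attainment Scaling paragraph fixes the starting score: "while -2 will be the baseline rate".
- **Section 10.3.2, Baseline Descriptive Statistics (Protocol).** Numerical variables get "means, standard deviations, and medians, range and interquartile range (IQR) for numerical variables". For the secondary outcomes, "change from baseline will also be reported (both absolute and percentage change". Goal attainment scores are in the list of examples there; headache-free days are not.
- **Measures to Minimize Bias and section 10.1 (Protocol).** The study is open-label and non-randomized, and it has no prespecified hypothesis.

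**The concern.** A count per month and a percentage change from baseline cannot both be the endpoint, and an analysis plan that follows one departs from the other.

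Of the two, the percentage is the weaker choice for this population. The entry criterion puts baseline headache-free days between 0 and about 15 in a 30-day month. At 0 the percentage does not exist, and the protocol gives no rule for that case. The participants who lose a value are those with the most frequent headache. At small non-zero baselines the percentage is dominated by the denominator: a gain of 3 days is +300% from 1 to 4 but +25% from 12 to 15.

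Goal attainment has a different fault. A score that starts at -2 has a negative denominator, so the sign of the percentage is reversed.

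The results are meant to inform a later randomized trial, and this trial has no control arm in which such artefacts would show up.

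**Working it through.** The protocol gives no effect size, standard deviation or distribution for headache-free days, so there is no figure of its own to reproduce. The distributions below are assumptions, shown over a range.

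**Inputs.** N = 20 (Sample Size Determination). Baseline range 0 to about 15 days (Inclusion Criteria). Goal baseline -2 (Goal Attainment Scaling). Means and medians both planned (section 10.3.2).

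**1. Zero baseline.** Let the baseline count X be Binomial(30, m/30), where m is the true mean number of headache-free days. Then P(X = 0) = (1 - m/30)^30, and the chance of at least one undefined participant among 20 is 1 - (1 - P(X = 0))^20.

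| m | P(X = 0) | At least one of 20 |
|---|---|---|
| 1 | 36.2% | about 100% |
| 2 | 12.6% | 93% |
| 3 | 4.2% | 58% |
| 4 | 1.4% | 24% |
| 5 | 0.4% | 8% |

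Example, m = 3: 0.9^30 = 0.0424, and 1 - 0.9576^20 = 0.58.

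**2. Mean percentage change with no effect.** Let the follow-up count Y be independent of X with the same m. Among participants with X > 0, the expected percentage change is 100 × (m × E[1/X | X > 0] - 1).

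| m | Mean % change | Median % change | Mean absolute change |
|---|---|---|---|
| 1 | -23% | -50% | 0.0 |
| 2 | +15% | 0% | 0.0 |
| 3 | +28% | 0% | 0.0 |
| 4 | +29% | 0% | 0.0 |
| 5 | +24% | 0% | 0.0 |
| 7.5 | +14% | 0% | 0.0 |
| 10 | +8% | 0% | 0.0 |

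The upward pull is easy to see in two participants who swap values. One goes from 1 to 2 days (+100%), the other from 2 to 1 (-50%). The mean percentage is (100 - 50)/2 = +25%, and the mean absolute change is 0. At m = 1 the sign flips because the zero baselines, which can only rise, are dropped.

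**3. Rates that differ between participants.** With true rates drawn from beta distributions capped at 15 days in 30 (average 3.0 to 9.0 days), the mean percentage change with no effect is about +9% to +17%, the median is 0, and the chance of at least one undefined participant falls from 99.5% to 7% as the average rises.

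**4. Goal scores coded from -2.** The percentage change to score s is 100 × (s - (-2))/(-2) = -50 × (s + 2), which is negative for every s above -2. A score of -1, the only other level the protocol names, gives -50%. If the scale continues to 0, +1 and +2 (an assumption), these give -100%, -150% and -200%. The absolute changes are +1, +2, +3 and +4, with the correct sign.

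**The case against.** The other side has a good deal to say.

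- **Weight of the endpoint.** It is secondary and descriptive, no hypothesis or decision rule depends on it, and individual data will be listed by measure and time point, so raw counts stay visible. This stands, and it limits the severity.
- **Absolute change may already be covered.** Section 10.3.2 promises absolute as well as percentage change for the secondary outcomes, and its list is introduced as examples. The omission of headache-free days does not show that they get percentage change alone. This stands too, but it does not settle which quantity is the endpoint or what happens at a zero baseline.
- **Medians are planned.** The false shift belongs to the arithmetic mean. A reader might infer that percentage change shows improvement whenever there is no effect; the median at 2 days or more, and the reversal at 1 day, contradict that.
- **A second goal measure exists.** The percentage toward a goal has no negative denominator and is unaffected. The reversal concerns only the -2-coded scores.

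Some wider readings are also tempting:

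- **Severe participants dropping out of the headache results.** This is true only of the percentage version.
- **How many have daily headache.** The protocol gives no figure, and it excludes new daily persistent headache and medication overuse headache, so a share such as 20% to 40% has no basis in it.
- **PedsQL.** No percentage change is set for it; scores are only compared with baseline.
- **PROMIS.** Percentages do depend on the starting level, but a 10-point fall is -14.3% from 70 and -16.7% from 60, which is minor. The T-score metric is mentioned only for Pain Interference.
- **Visit windows of ±5 days.** Intervals of 20 to 40 days would matter only if counts ran from visit to visit, which the protocol does not say. The derivation of a month can be left to the analysis plan.

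**Conclusion.** The point holds in three parts.

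1. The synopsis and the objectives table define the first secondary endpoint differently. This rests on the text alone.
2. Percentage change is undefined for some participants whom the protocol admits. That the case can occur follows from the entry criterion; how often (24% to 93% for at least one of 20 at true means of 4 down to 2 days) rests on the binomial assumption. The distortion of the mean rests on the same assumption.
3. Percentage change applied to goal scores that start at -2 reports every improvement as a decrease. This is arithmetic and needs only the stated baseline.

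The primary safety objective is not affected. This is a should-fix correction of wording, to be made before the analysis.

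**What to change.** - **Synopsis and Objectives and Endpoints table.** State one endpoint in both: absolute change in headache-free days per month from the run-in month to each treatment month. Preferably scale it to completed diary days: headache-free days ÷ completed diary days × 28. Naming the run-in month matters because the diary is only assigned at visit 1, so that month is the only one it covers before dosing.
- **Section 10.3.2.** Name headache-free days among the outcomes reported with absolute change. Report the -2-coded goal attainment scores as absolute change only.
- **Objectives and Endpoints table, fifth and sixth items.** Take goal attainment scaling out of the percentage-change list and keep the percentage toward a goal as a separate, separately named measure.

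The cost is a few lines of wording and no change to data collection. The one loss is that a percentage figure for headache-free days can no longer be quoted.

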| Statistical Methodology | *Sample Size determination:*  Precedent suggests that a power calculation is not appropriate for a dose-finding study. The study site and the number of planned dose escalations are standard for clinical trials.  *Populations for Analyses:*  We will complete an intent to treat analysis. All participants who received the investigational product for at least one month will be included in the analysis to ensure that these data would be likely to represent the effects of the study intervention.  *Safety Analyses:*  The severity, frequency, and relationship of AEs to study intervention will be presented by System Organ Class (SOC). The start date, stop date, severity, relationship, expectedness, outcome, and duration of each AE will be reported. Serious treatment-emergent AEs will be presented either in a table or a listing.  *Baseline and Descriptive Statistics:*  We will perform the descriptive statistics to describe baseline characteristics and other outcomes. The proportions and frequencies will be used to categories the categorical variable. The mean, median, range or standard deviations will be used to categories the continuous endpoints. Subgroup summarization based on dose level or other criteria may also be conducted. Median concentrations of CBD, THC and the major metabolites will be reported with ranges for each sampling time point. The ratio of parent to metabolites will be reported to provide estimates of the variability in cannabinoid metabolism.  *Sub-Group Analyses:*  We will perform prespecified subgroup analysis of primary and secondary outcomes-based sex and dose. |

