# STUDY INTERVENTION DISCONTINUATION AND PARTICIPANT DISCONTINUATION/WITHDRAWAL

## Dose limiting toxicity and Discontinuation of Study Intervention

Adverse events are categorized using the Common Terminology Criteria for Adverse Events (CTCAE version 5.0 dated 27 Nov 2017). If any of the following occur the participant will not move up to the next dose level (dose limiting toxicities):

1. Parental/youth report complaints of moderate mood elevation defined as exaggerated feelings of well-being which is disproportionate to the events and stimuli (Euphoria Grade 2)
2. Somnolence Grade 2 which includes moderate sedation (sleepiness and drowsiness) that limits instrumental activities of daily living
3. Cannabis-attributed diarrhea, Grade 2 or more defined as an increase of 4 - 6 stools per day over baseline; moderate increase in ostomy output compared to baseline; limiting instrumental activities of daily living
4. Unexplained tachycardia (w/out pain, fever, anemia etc.) requiring medical intervention
5. Unexplained hypotension requiring medical intervention
6. Non-infectious conjunctivitis Grade 2 defined as moderate decrease in visual acuity (best corrected visual acuity 20/40 and better or 3 lines or less decreased vision from known baseline) characterized by inflammation, swelling and redness to the conjunctiva of the eye.
7. Serious adverse events requiring hospitalization
8. Discretion of the participant, physician, or parents

Discontinuation from the study intervention does not mean interruption from the study, and remaining study procedures should be completed as indicated by the study protocol.

There will be no replacement of the study participants who were administered the investigational product, withdraw from the study, and lose follow-up (after signing an informed consent form). The main reason for the withdrawal of participants from the study will be noted in the participant's Case Record Form (CRF). The site investigator should contact the participants who fail to report during the follow-up visits which will be documented in the CRF.

Adverse events (AEs) and SAEs (Serious Adverse Events) will be reported according to Health Canada and Institutional regulations and reviewed by the data safety monitoring board (DSMB). The DSMB will hasten safety review if death is deemed related or potentially relevant to CBD-enriched CHE used in the study as the investigational product.

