## Sample Size Determination

The CAN-CHA trial is a tolerability study designed to identify a safe dose of a cannabis product in adolescents with chronic headache. Because of the within-participant study design, a sample size of 20 study participants should provide a reasonable characterization of the pattern of adverse event frequency and severity as dosage increases. To provide more generalizable data, we will recruit these 20 study participants across three chronic pain programs in Halifax, Vancouver, and Toronto.

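### Troughs are collected to study pharmacokinetic linearity, but the stated medians do not by themselves address it, and they flatten when participants are held at a dose

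*Protocol*

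**What the plan says.** Objectives and Endpoints (Exploratory) sets the aim: "To investigate the relationship between the dose-escalation and steady-state trough levels of bioactive cannabinoids". The justification beside it reads "It is an important measure to study the linearity of the pharmacokinetics of the drug product" and goes on to how metabolism changes over time and differs between individuals.

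Section 10.3.2 (Baseline Descriptive Statistics) gives the analysis: "Medians, ranges and IQR, will be provided for the concentrations of CBD, THC and the primary metabolites at each sampling point". It adds "Summaries will be provided both overall and by dosage level" and a summary of parent-to-metabolite ratios. The Synopsis has a shorter version: "Median concentrations of CBD, THC and the major metabolites will be reported with ranges for each sampling time point". No slope, dose-normalised trough or within-participant contrast of concentration against dose is stated.

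Two other rules matter. Under Dose limiting toxicity and Discontinuation of Study Intervention, for a list of toxicities and at the discretion of participant, physician or parents: "If any of the following occur the participant will not move up to the next dose level". Footnote a of the Schedule of Activities and the withdrawal section keep participants who stop the product in follow-up to visit 7; the footnote includes bloodwork.

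**The concern.** Linearity asks whether a person's trough rises in proportion to that person's dose. The trial collects what is needed to answer this, a trough from each participant at up to four dose levels. A median per visit or per dose level makes no use of the pairing. Large differences between people then enter the comparison as noise.

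The hold rule adds a second problem. At later visits some participants may still be on a lower dose, or on none, so a median by sampling point mixes doses. A median by dose level avoids the mixing, but the upper levels contain only those who were escalated. At stake is whether the dose-to-trough objective gets a sound answer. The primary safety objective and the dosing decisions do not depend on it.

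**Working it through.** The protocol gives no linearity estimate, variability or hold rate, so there is no figure to reproduce. The check is a simulation under stated assumptions, with closed forms where they exist.

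**Inputs from the protocol**
- Mid-range doses of 0.3, 0.5, 0.7 and 0.9 mg/kg/day (Dosing and Administration); top/bottom ratio 0.9/0.3 = 3.0.
- 20 participants.
- Troughs before each escalation and at the end of treatment (Cannabinoid and metabolite evaluation). Dosing starts the day after visit 2, so the four on-treatment troughs fall at visits 3 to 6.
- Rounding to 1 mg hardly matters. The ratio stays 3.0 at 40, 50, 60 and 80 kg. The 24 kg example gives 22/7 = 3.14.

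**Assumptions, not in the protocol**
- Lognormal troughs, exactly proportional to dose (log-log slope 1).
- Between-participant CV 60-90% and within-participant CV 30-40%, with σ = √ln(1+CV²).
- A held participant stays on the last dose and is still sampled. Off-product samples were not simulated.
- 4,000 simulated trials per setting.

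**Step 1: precision with no holds.** The sum of squares of log dose about its mean is 0.377 + 0.011 + 0.054 + 0.235 = 0.677. The SD of the within-participant slope is σ_w/√(20 × 0.677) = σ_w/3.68.
- CV 30%: 0.294/3.68 = 0.080.
- CV 40%: 0.385/3.68 = 0.105.

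The slope fitted through the four medians has a simulated SD of 0.13-0.17. Both average 1.00, so medians are unbiased here and only less precise.

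**Step 2: medians by sampling point, holds unrelated to exposure.** A 10% chance of a hold at each of three steps gives 1 − 0.9³ = 0.271, and 0.271 × 20 = 5.4 held. The slope of the medians averages 0.85-0.86. With about 1 held it averages 0.97. The within-participant slope averages 1.00 in both cases. A separate run with 30% held (between-participant CV 50-100%, within-participant CV 30%) gives a last-to-first ratio of 2.49-2.55 instead of 3.0.

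**Step 3: medians by dose level.**
- Holds unrelated to exposure, 30% held: ratio 2.99-3.02, no bias.
- Holds rising with exposure (per-step hold probability logistic, coefficient 1.5 on the participant's log-exposure deviation): slope about 0.94-0.97 with 1-2 of 20 held and 0.77-0.88 with 6-7 held. The within-participant slope averages 1.00 (SD 0.09-0.12 in the heavier case).
- These figures use one sample per participant per level. Counting a held participant's repeat samples at that level as well lowers the heavier case to 0.60-0.79.

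**Closed-form check of step 3.** If the fraction f with the highest exposure never reaches the top level, the ratio is 3 × exp(σ_b × z((1−f)/2)). At CV 80% and f = 0.2, σ_b = 0.703 and z(0.40) = −0.253. The ratio is 3 × exp(−0.178) = 2.51 and the slope is 1 − 0.178/1.099 = 0.84. Over CV 50-100% and f = 20-40% the ratio runs from 2.66 down to 1.94.

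**The case against.** The strongest reply is that this belongs to the SAP, which is not at hand. The objective is exploratory, no hypothesis is specified, the medians stand under a descriptive heading, and nothing excludes a paired analysis. Section 10.3.4 lists individual data by time point, so the pairing is not lost. A dose-exposure-response comparison is also planned. This carries weight. But the protocol is not silent: it names a purpose and a summary, and the summary does not serve the purpose. Listings are data, not an estimate. The exposure-response comparison relates concentrations to adverse events and secondary endpoints, not to dose.

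The second reply is that the bias rests on assumed inputs. This stands. The protocol expects the maximum CBD dose to be under a tenth of that recommended in earlier paediatric studies and foresees no adverse psychoactive reactions from the THC, so holds may be few. Discretionary holds need not follow exposure. They would leave medians by dose level unbiased, though not medians by sampling point.

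Third, the within-participant slope is not wholly immune. If holding follows exposure at the particular visit and not a stable trait, it averages 1.03-1.04.

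A reader might infer more than the text supports:
- That medians cannot estimate linearity. They recover slope 1.00 when all escalate, and by dose level when holds are unrelated to exposure.
- That the protocol promises a test of linearity. It speaks of studying it.
- That the sample-size rationale, "Because of the within-participant study design", is contradicted. That sentence concerns adverse events, not pharmacokinetics.
- That exposure in the future RCT would be under-predicted. No section uses these medians for that purpose; what carries forward is a tolerated dose.

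**Conclusion.** The point holds in limited form. The stated medians do not by themselves address the linearity for which the troughs are collected, and they are less precise than a within-participant slope even when nobody is held. With holds, medians by sampling point understate the slope whatever the cause. Medians by dose level do so only if holding rises with exposure.

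The size depends on hold rates, variability and an exposure-toxicity link that the protocol does not give. With 1-2 of 20 held, the shift of about 0.03-0.06 in slope is well inside one SD (0.13-0.17). With 5-7 held it is about 0.12-0.23, of the order of one SD. This is a cheap improvement to an exploratory analysis and not a flaw in the trial's main conclusions.

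**What to change.** In section 10.3.2, for the exploratory dose-to-trough objective, add for each analyte a within-participant power model: log trough on log dose actually taken, with a participant effect, using on-treatment samples only. Report the slope with a 90% CI as an estimate and not as a formal test. With no holds, the half-width under the assumed CVs would be about 1.645 × 0.080 = 0.13 to 1.645 × 0.105 = 0.17.

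Plot dose-normalised troughs per participant, which also serves the stated interest in differences between individuals. Keep the medians, ranges and IQR as description, grouped by the dose actually taken, and align the Synopsis.

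The cost is one small model per analyte. No new data, visits or samples are needed.
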